**Conclusions:**

This analysis will help identify mechanisms of skin damage following repeated shear stress at the heel, furthering our understanding of superficial pressure ulcers. It will also establish physiological and perceptual thresholds for the protective effects of cooling from shearing-induced damage at the heel.

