It is also important to note that physiological and perceptual tolerance to pressure and shear at the skin interface may also vary as a function of age and comorbidities [30], which could in turn diminish the therapeutic efficacy of cooling. For example, aging-induced changes in skin biophysics and morphology [31], as well as decreases in both reflex cutaneous vasoconstriction and density of thermoreceptors [32], are likely to modulate the thermoregulatory and perceptual sensitivity of the skin to localized cooling. Similarly, autonomic and sensory dysfunctions resulting from SCI manifest in impaired control of skin blood flow and lack of sensation below the injury level [33,34].

Based on the evidence above, this study protocol aims to investigate (1) how different levels of localized cooling influence the skin’s microvascular, inflammatory, structural, and perceptual responses to repeated pressure and shear loading at the heel; and (2) how metabolic, immunological, biophysical, and perceptual pathways underlying the effects of localized cooling on skin tolerance to shear are modulated by aging and SCI. The research that will be delivered via this protocol will be both important in improving scientific knowledge and timely to societal demands, as it will support the development of user-centered approaches to maintaining skin tissue viability via evidence-based therapeutic cooling.

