## Methods

### Overview

Participants will attend 3 experimental sessions separated by a minimum of 24 hours in the Clinical Academic Facility located at Southampton General Hospital (Southampton, United Kingdom). During the sessions, participants will place the center of their posterior heel on a custom-built friction rig with an integrated thermal plate to undergo a standardized protocol eliciting repeated pressure and shear force. The study will use a randomized crossover design involving 3 plate temperatures: 36 ºC (no cooling), 24 ºC (mild cooling), or 16 ºC (strong cooling). Microclimate conditions at the interface between a loaded skin site at risk of pressure ulcer (eg, the sacrum) and a support surface (eg, a mattress) are commonly associated with skin temperatures of approximately 38 ºC. Following pilot testing, some participants (n=2) found a 38 ºC plate temperature to be borderline uncomfortable, so we decided to reduce the plate temperature to 36 ºC to improve thermal tolerability in the no cooling condition. The rationale for using 2 levels of cooling was 2-fold: first, prior research investigating localized cooling on tissue viability in animal models [17,18] used cooling interventions at 25 ºC, demonstrating the benefit of reduced skin temperature in preserving tissue viability. Second, one of the main aims of the study is to examine how different levels of cooling may influence the biophysical properties of the skin and perceptual thermal tolerances of both mild (24 ºC) and strong (16 ºC) cooling.

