The sample size justification for this protocol is based on the power calculations from Gordon et al [35], using changes in the peak hyperemic response, which is a robust, repeatable response. Specifically, we will recruit a minimum of 18 participants per group, with target recruitment of 35 individuals, to allow for sufficient statistical power and to account for up to 50% dropout. Participants will be screened for study participation using a set of inclusion and exclusion criteria. The young and healthy participants will be aged 18 to 35 years and the older and healthy participants will be aged 55 to 70 years. The participants presenting with SCI will have an injury level within T1 to S1. The younger and older healthy groups will undertake regular physical activity (1-3 times per week), be nonsmokers and nonvapers, and be free from comorbidities that would preclude them from taking part, such as hypertension or Raynaud's disease. Both male and female participants will be recruited for a subanalysis on the influence of sex; we will also recruit individuals with different skin tones, ranging from light to dark, as assessed by the Fitzpatrick scale [36]. Stratified skin sampling will be used to determine whether there is an influence of skin tone on pressure and shear tolerance at the skin of the heel.

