### Ethical Considerations

This project will recruit and test healthy individuals aged 18 to 70 years as well as individuals with SCI. The project will be conducted in line with the Southampton University Code of Practice for Research, complying with the Declaration of Helsinki. Written informed consent will be obtained from participants, as will relevant personal information (eg, perceptual skin sensitivity to cooling). Participants will have the unconditional right to withdraw from the study at any point.

Data management will adhere to the University of Southampton’ policy on data quality, which forms part of the University’s Information Governance Framework, complying with the requirements of the Data Protection Act 2018 and the University of Southampton’s Ethics Committee (Ethics and Research Governance Online; ERGO) policies. This project involves human participants and will be conducted in line with the university’s policy on the ethical conduct of research and studies involving human participants and the Medical Research Council’s policies on ethics and data sharing. Data will be fully anonymized at the earliest opportunity and before being made available with open access in the university’s data repository. All data that supports publication will be deposited and will be citable using a persistent identifier (DOI). Research findings will be published in high-quality, peer reviewed academic journals.

Participants will be eligible for compensation for their time upon successful completion of an experimental trial in the form of retail vouchers (maximum compensation value: £576 [US $785]). All experimental methods and measurements will be noninvasive, posing low risks to participants. However, mitigation measures are in place to manage any risks that may develop, including on-going skin temperature monitoring, checks of subjective well-being, and active skin rewarming following the cooling stimuli. The skin will also be checked for blanching erythema at regular intervals. Ethical approval for the stated measurements and procedures has been granted by the University of Southampton’s Ethics Committee (ERGO 88984).

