#### Perceptual Assessments

Participants’ local thermal and comfort sensations will be assessed via Likert scales to establish time-dependent changes in subjective perceptions of cooling [47]. The Likert scales for thermal sensation, thermal comfort, and thermal acceptance were created based on the recommendations of Schweiker et al [48], using a ruler to draw a 100-mm horizonal line with evenly spaced anchors. Thermal sensation is measured on a 7-point scale from 1 (cold) to 7 (hot), with 4 as neutral. Thermal comfort used a 5-point scale ranging from 1 (comfortable) to 5 (extremely uncomfortable), and thermal acceptance used a 4-point scale ranging from 1 (clearly acceptable) to 4 (clearly unacceptable). Perceptual sampling will occur before and after the shear protocol (Figure 2).

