### Statistical Analyses

Data will be assessed for normality of distribution with the Kolmogorov-Smirnov test. Within- and between-subject mean differences (n=35 with 95% CIs) as a function of mechanical stimulus temperature (ie, 36 ºC, 24 ºC, and 16 ºC), time (ie, varying levels depending on the variables’ sampling rate), and participant group (ie, young, older, SCI) will be analyzed. These independent and interactive effects will be assessed by means of 3-way mixed model ANOVAs (or Friedman tests) for biomarker expression, skin structural properties, biophysical properties (ie, imaging parameters), subjective thermal perceptions, and kinetic CoF. Post hoc analyses will be performed between shear stimulus temperatures, time, and participant groups based on the presence of main effects and using the Tukey test. Group-related covariables associated with sex, skin tone, and clinical status (applicable to SCI participants only) will be considered in all analyses to interpret the proportion of variance unexplained by the main effects (ie, temperature, time, and group) and their interactions.

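### Heel ratings of thermal sensation, comfort and acceptance are pooled across sensate and possibly insensate SCI participants, so a flatter SCI response cannot be told apart from better tolerance of cooling

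*Protocol article*

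**What the plan says.** - **Site and rating.** Under Overview, "participants will place the center of their posterior heel on a custom-built friction rig". Under Perceptual Assessments, "Participants’ local thermal and comfort sensations will be assessed via Likert scales to establish time-dependent changes in subjective perceptions of cooling". Comfort uses a "5-point scale ranging from 1 (comfortable) to 5 (extremely uncomfortable"; acceptance runs from 1 (best) to 4 (worst); sensation runs from 1 to 7 with 4 as neutral. No response option for a participant who cannot feel the plate is described.
- **SCI cohort.** Under Participants, "The participants presenting with SCI will have an injury level within T1 to S1". The Introduction says SCI brings "impaired control of skin blood flow and lack of sensation below the injury level".
- **Analysis.** Statistical Analyses names the groups as young, older and SCI. It lists "biophysical properties (ie, imaging parameters), subjective thermal perceptions, and kinetic CoF" among the outcomes of the three-way mixed ANOVA (or Friedman test), with Tukey comparisons between groups. Clinical status is to be considered as a covariable that exists only in the SCI group; it is not defined.
- **Information collected.** Ethical Considerations says the study will obtain "relevant personal information (eg, perceptual skin sensitivity to cooling". The article gives this no role in the analysis and does not say that it refers to the heel.
- **Intended inference.** The second aim in the Introduction asks how ageing and SCI alter perception of cooling. The abstract's Conclusions add: "It will also establish physiological and perceptual thresholds for the protective effects of cooling".

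**The concern.** A comfort or acceptance rating means something only if the rater can feel the stimulus. By the article's own account some SCI participants may not feel it, because for most of the T1 to S1 range the heel lies below the lesion. Their ratings nevertheless enter the same model, on the same scales, as those of sensate volunteers.

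A participant without heel sensation may mark the favourable end of the scale, mark neutral, guess, or leave the item blank. In none of these cases is the answer a graded response to temperature. The SCI group mean then depends on two things at once: how people who feel the plate respond, and how many people do not feel it. The second also dilutes any temperature effect averaged over the three groups.

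At stake is the reading of the perceptual results in the cohort with impaired sensation. A small SCI response to 16 °C could come from absent sensation, from tolerance, or from both, and the planned analysis does not separate them.

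**Working it through.** **1. The article's own figure.** The only reproducible number is the recruitment target: 18 / (1 − 0.5) = 36 against the stated 35 (35 × 0.5 = 17.5). It agrees within rounding. The point does not depend on it; 18 and 35 serve below only as group sizes.

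**2. Effect of mixing on the temperature response.** Let Δ be the mean change in a rating between 36 °C and 16 °C among people who can feel the plate, and f the insensate share of the SCI group. Assume that insensate participants give the same rating at every temperature and that sensate SCI participants respond like the healthy groups.

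- SCI effect = (1 − f) × Δ
- Effect pooled over three equal groups = [Δ + Δ + (1 − f)Δ] / 3 = (1 − f/3) × Δ

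Neither f nor Δ is in the article. Both are assumptions:

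| f | SCI effect, Δ = 1 | Δ = 2 | Δ = 3.5 | Pooled effect as share of Δ |
|---|---|---|---|---|
| 25% | 0.75 | 1.5 | 2.6 | 0.92 |
| 50% | 0.50 | 1.0 | 1.75 | 0.83 |
| 75% | 0.25 | 0.5 | 0.9 | 0.75 |
| 100% | 0 | 0 | 0 | 0.67 |

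**3. Why the cause cannot be recovered.** Let sensate SCI participants respond at a fraction t of the healthy effect. The observed ratio of SCI to healthy effect is (1 − f) × t. A ratio of 0.5 arises from f = 50% with t = 1 (loss of sensation only), from f = 0 with t = 0.5 (a genuinely weaker response), or from f = 25% with t = 0.67 (0.75 × 0.67 ≈ 0.5). Without knowing who can feel the heel, these cannot be distinguished.

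**4. Illustration of a between-group contrast.** Comfort at one temperature, 5-point scale, ratings drawn as a rounded and clipped normal with SD 1. Sensate participants in both groups have mean m, and insensate SCI participants score 1. SCI is compared with one healthy group by a Mann-Whitney test at two-sided 0.05, with 2,000 runs per setting. This is simpler than the planned model, and f, m, SD and the score of 1 are all assumptions. The expected shift in the SCI mean is −f × (m − 1). For m = 3:

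| f | Shift in SCI mean | Runs significantly favouring SCI, n = 35 | n = 18 |
|---|---|---|---|
| 0 | 0 | 2% | 2% |
| 25% | −0.5 | 40% | 23% |
| 50% | −1.0 | 95% | 71% |
| 75% | −1.5 | 100% | 99% |
| 100% | −2.0 | 100% | 100% |

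For m from 2 to 4 and f from 25% to 100%, the range is 25% to 100% at n = 35 and 14% to 100% at n = 18. With f = 0 it stays at 2% to 3%, close to the nominal one-direction rate.

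**5. The covariable.** Clinical status has no values in the healthy groups. It can describe variation within SCI, but by itself it cannot show how much of an SCI-versus-healthy difference is due to absent sensation. Nor does the article say that it records heel sensation.

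**The case against.** The strongest reply is that the group difference is intended. The second aim asks how SCI changes perception of cooling, and the Introduction gives sensory loss as a reason for studying this cohort. A flatter SCI response answers that aim. For adherence to a cooling device, absence of felt discomfort is also a real finding. This stands: taking SCI out of the perceptual analysis would cut a stated aim. It does not rescue the pooled mean, because the aim is served only if loss of sensation and change in comfort are shown separately.

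A reader might go further and infer that the plan will report insensate ratings as better tolerance, with a near-certain group by temperature interaction. The article does not support that. Its Objective and Conclusions do speak of perceptual tolerance and thresholds, but nowhere does it say that unfelt cooling will be counted as tolerated cooling, and the threshold sentence does not mention SCI. Completeness of injury is not stated, so f could be small; at f = 25% the illustration gives 40% or 23%, far from certain. Guessing or missing answers would add noise or gaps instead of a directional shift.

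A condensed article may also leave detailed eligibility and the definition of clinical status to the full protocol. That is fair, and their absence is not the criticism. The criticism is that the article fixes the outcome, the three groups, the model and the contrasts in a way that sits badly with its own statement about sensation.

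**Conclusion.** The concern holds in a limited form. As written, the perceptual analysis combines participants who can and cannot feel the heel, so the SCI mean, the SCI-versus-healthy contrasts and the pooled temperature effect on comfort and acceptance depend partly on an unreported insensate share. A flatter SCI response could not be attributed to tolerance or to loss of sensation.

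The size depends on f. Under the constant-rating assumption the SCI effect is (1 − f) of the sensate effect and the pooled effect is (1 − f/3) of it; a direction favouring SCI further assumes that insensate participants choose the favourable end. None of these quantities is given in the article. The conclusion does not extend to dropping SCI from the perceptual aim, nor to the blood flow, biomarker, imaging, conductance or friction outcomes, none of which relies on the participant's report. It is worth settling before the perceptual data are analysed.

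**What to change.** 1. Keep SCI in the study of how injury alters perception, as the second aim requires.
2. Classify each SCI participant by preserved thermal sensation at the heel. Use the sensitivity information mentioned under Ethical Considerations if it covers the heel; if it does not, a heel-specific record is needed.
3. Present SCI ratings of sensation, comfort and acceptance by that status.
4. Base the between-group comfort and acceptance contrasts, and the perceptual-threshold conclusion, on participants with preserved heel sensation.
5. Report insensate participants separately as loss of sensation, not as comfortable, accepting or neutral.

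**Cost.** This is mainly a change to the analysis text, plus a sensory record where none exists for the heel. The sensate SCI subset would be 35 × (1 − f): about 26, 17 or 18, or 9 for f = 25%, 50% or 75%. From the minimum of 18 it would be about 13 or 14, 9, or 4 or 5. Perceptual contrasts involving SCI lose precision and may have to be descriptive if f is high. The recruitment target is unaffected, since it rests on peak hyperaemic response.

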**Methods:**

The protocol will be tested on individuals of different age, sex, skin tone, and comorbidities, using a repeated measures design. Three cohorts will be recruited: (1) young and healthy (n=35), (2) older and healthy (n=35), and (3) with spinal cord injury (n=35). Participants will complete 3 testing sessions using a custom-built shearing rig with integrated thermal plate, during which the posterior aspect of the heel will be exposed to a standardized mechanical stimulus to elicit repeated pressure and shear loading. The experimental condition of each session will be determined by the temperature of the thermal plate, which will be set to either 36 °C (no cooling), 24 °C (mild cooling), or 16 °C (strong cooling). Continuous measurements will include kinetic coefficient of friction (CoF) and skin blood flow (via laser Doppler flowmetry; 40 Hz). Pro- and anti-inflammatory biomarkers in skin sebum (via Sebutape), structural skin properties (via optical coherence tomography), skin conductance (in microsiemens) and ratings of thermal sensation, comfort, and acceptance (via Likert scales) will also be assessed before and after the shear stress protocol.

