**Figure 1 figure1:**
[figure not shown]
Experimental set up. The foot and ankle are supported by an orthotic brace and ankle support to standardize positioning while minimizing movement during the shearing protocol.

A series of measurements that run continuously or during discrete time points will be taken (Figure 2). First, baseline assessments, including structural and functional imaging of the posterior heel skin, will be captured using optical coherence tomography (OCT). This will be followed by sampling of skin sebum at the heel for subsequent biomarker analysis, using an established methodology involving a 2-minute application time and tweezer extraction to avoid cross contamination [38]. To provide an index of baseline local skin hydration, a capacitance meter will then be placed on the heel to measure skin conductance (in microsiemens). After the baseline measurements are completed, participants will place the heel on the thermal plate of the shearing rig [13]. The temperature of the aluminum thermal plate (22 × 16.7 cm) is controlled by a set of Peltier elements, and when applied to the skin, allows for the manipulation of local skin temperature (range 0 °C to >50 °C; variable temperature rates under PID control [Daisylab; MC Computing]). An optical fiber is integrated in the center of the plate through a 1-mm hole flush to its surface, allowing for the monitoring of skin blood flow via laser Doppler flowmetry (LDF) when the heel is static. An integrated force plate and low resistance trackway allow the recording of both normal and tangential forces (in newtons), respectively. The friction rig is interfaced with an analogue-to-digital data acquisition unit (MC Computing), sampling plate surface temperature (°C), normal forces, and tangential forces at 33 Hz. The kinetic coefficient of friction (CoF) according to Amonton’s law [39] can be estimated as the ratio of tangential to normal force and defined as the resistance generated from 2 surfaces rubbing against each other [40].

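### Post hoc comparisons are tied to main effects, although aim 2 is an interaction for every outcome and aim 1 is one for the outcomes with an untreated baseline

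*Protocol article*

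**What the plan says.** The Introduction sets two aims. Aim 1 is "how different levels of localized cooling influence the skin’s microvascular, inflammatory, structural, and perceptual responses to repeated pressure and shear loading at the heel". Aim 2 is "how metabolic, immunological, biophysical, and perceptual pathways underlying the effects of localized cooling on skin tolerance to shear are modulated by aging and SCI".

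The Statistical Analyses section names temperature, time and participant group as factors and continues: "These independent and interactive effects will be assessed by means of 3-way mixed model ANOVAs (or Friedman tests". Interactions are therefore tested in the ANOVA. The follow-up rule comes next: post hoc analyses are "performed between shear stimulus temperatures, time, and participant groups based on the presence of main effects and using the Tukey test". Interactions are not named as a trigger, and no comparison within a time point or within a group is described.

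On timing, the abstract says that biomarkers, OCT, skin conductance and perceptual ratings "will also be assessed before and after the shear stress protocol". Experimental Procedures places the OCT, sebum and conductance baselines before plate contact: "After the baseline measurements are completed, participants will place the heel on the thermal plate of the shearing rig". The post-test values of these three follow the 10 shear repetitions. Friction is recorded on the temperature-controlled plate during shear. The blood flow baseline is the mean over the 60-second thermal preconditioning period, also on the plate.

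**The concern.** The follow-up rule does not match the questions asked.

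- **Aim 2, all outcomes.** Whether aging or SCI changes the effect of cooling is a temperature-by-group question (temperature-by-group-by-time for pre/post outcomes). A group main effect says that groups differ on average over temperatures. A temperature main effect says that temperatures differ on average over groups. Neither says that the cooling effect differs between groups.
- **Aim 1, OCT, biomarkers and conductance.** Plate temperature cannot influence a value taken before the heel touches the plate. The cooling effect is in the post value alone, so the aim is a temperature-by-time question. The temperature main effect averages an untreated and a treated time point.

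Two things are at stake. A significant interaction without a temperature main effect leaves no planned comparison of temperatures, and any later one would look data-driven. If the trigger does fire, the marginal comparison reports a cooling effect at half its size.

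**Working it through.** **The plan's own figure.** The document gives no power for any temperature contrast or interaction. Its only related figure is recruitment: 18 per group with up to 50% dropout gives 18 / 0.5 = 36, against a stated target of 35 (35 × 0.5 = 17.5). This agrees to within one participant. The basis of the 18 lies in the companion protocol and cannot be checked here.

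**Inputs from the document.** Three temperatures, three groups, 18 (minimum) to 35 (target) per group. OCT, sebum and conductance have one untreated pre value and one post value per session.

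**Assumptions.** Two-sided 5% level; equal pre and post variance s²; no expected baseline difference between sessions; post-test effect d for 16 vs 36 °C. The pre-post correlation within a session is r, after stable participant differences are removed (they cancel in within-participant contrasts). The document gives no r, so a range is shown.

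**Size of the estimate.** The main-effect contrast averages a pre difference of 0 and a post difference of d: (0 + d)/2 = d/2. This holds for every r.

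**Signal to noise, 16 vs 36 °C within a participant.**
- Main effect: expectation d/2. The session mean has variance s²(1+r)/2, so the difference of two sessions has variance s²(1+r).
- Temperature-by-time (change) contrast: expectation d. The session change has variance 2s²(1−r), so the difference has variance 4s²(1−r).
- Ratio, main effect to change contrast: [d/(2s√(1+r))] / [d/(2s√(1−r))] = √((1−r)/(1+r)).

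**Power.** With n = 35 and a paired t test, 80% power for the change contrast needs a standardized effect of 0.487. Multiplying by the ratio gives the main effect:

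| r | ratio | standardized effect | power of main effect |
|---|---|---|---|
| 0 | 1.000 | 0.487 | 80% |
| 0.1 | 0.905 | 0.441 | 72% |
| 0.3 | 0.734 | 0.358 | 54% |
| 0.5 | 0.577 | 0.281 | 37% |
| 0.7 | 0.420 | 0.205 | 22% |

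With n = 18 the powers are the same to within 0.2 percentage points.

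**Check on the full layout.** Three groups, three temperatures, pre and post, post shifts of 0, −d/2 and −d at 36, 24 and 16 °C, and d set so that the temperature-by-time F test has 80% power. The temperature main effect then has 80%, 52%, 34% and 20% at r = 0, 0.3, 0.5 and 0.7. In simulation (2000 runs per scenario, equal effect in all groups), an interaction was significant while the temperature main effect was not in 38–40%, 52–53% and 64–65% of runs at r = 0.3, 0.5 and 0.7.

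**Aim 2.** With d set so that the three-way term has 80% power:
- Cooling acts in one group only: the temperature main effect is significant in 34%, 22–24% and 14% of runs at r = 0.3, 0.5 and 0.7.
- Opposite effects in two groups, none in the third: about 5%, the nominal level, at each of these r.

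**The case against.** The strongest reply is that the ANOVA itself tests the interactions, so both aims are covered at the omnibus step. That stands. A reader might infer from the follow-up rule that real cooling effects will be missed altogether. The document does not support this: an effect can show as a significant interaction. What is absent is the planned step that locates it.

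A second reply is that halving the effect need not cost power against the plan's own temperature-by-time test. That also stands. At r = 0 there is no loss, and at negative r the main effect is the more powerful test. In a crossover, r can lie well below the raw pre-post correlation, because stable participant differences drop out. A comparison with baseline-adjusted analysis of covariance would show a larger loss, but the protocol does not plan that analysis, so it is not the yardstick for the current rule. The half-size estimate does not depend on r.

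Third, the dilution is limited in scope. It does not apply to friction, whose values are all taken on the temperature-controlled plate, or to blood flow, whose baseline is already at plate temperature. For perceptual ratings the text does not make clear whether the first rating precedes plate contact, so dilution is not established there.

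Finally, naming Tukey does not fix the error term. Tukey-adjusted contrasts can be taken from a mixed model, so a reader should not infer that the choice of Tukey is itself an error.

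**Conclusion.** The point holds as a mismatch between the follow-up rule and the aims, and should be fixed. For every outcome, aim 2 is an interaction for which no follow-up is stated. For OCT, biomarkers and conductance, the comparison that the rule triggers estimates half the post-test cooling effect; this follows from the measurement schedule and needs no assumption about r. The trigger's loss of power does depend on r: from none at r = 0 to about 22% against 80% at r = 0.7. With opposite effects in two groups it fires at about the 5% level. These powers rest on the assumed 5% two-sided level, equal variances and effect patterns listed above, none of which the document gives.

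**What to change.** Drop the rule that follow-up depends on main effects and pre-specify the contrasts that answer the aims.

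- **OCT, biomarkers, conductance (aim 1):** 24 vs 36 °C and 16 vs 36 °C on post values adjusted for the session's own baseline, or on change.
- **Friction (aim 1):** keep the temperature main effect. Do not replace it with temperature-by-repetition contrasts, which would be zero if cooling lowered friction equally at all 10 repetitions.
- **Blood flow:** do not treat the on-plate preconditioning baseline as untreated, since subtracting it may remove part of the cooling effect.
- **All outcomes (aim 2):** test the differences in these contrasts between older and young, and between SCI and controls, naming the control group.
- **Estimation:** take the contrasts from the mixed model with its within-subject covariance and a stated multiplicity adjustment, Tukey-type or Holm.
- **Perceptual ratings:** state whether the first rating precedes plate contact, then place them under the matching rule.

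The smallest acceptable change is to let significant interactions also trigger comparisons of temperatures at post-test and within group.

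The cost is analysis wording only, since all baselines are already collected. The downside is that marginal main effects become descriptive for OCT, biomarkers and conductance. As analysis is described as ongoing, the change should be recorded before results by temperature are seen.
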